## Abstract

To evaluate the efficacy of acupuncture combined with rehabilitation training in patients with intensive care unit (ICU)-acquired muscle weakness (ICUAW), a single-blinded, randomized, sham-controlled clinical trial is designed for execution. In total, 56 participants with ICUAW will be randomly assigned to the treatment and control groups with 28 participants in each group. The participants will be treated with acupunctures or sham procedures at LI15, LI11, ST36, GB34, and ST31, 5 times per week for a total of 20 sessions in 4 weeks while they will receive rehabilitation training. Patients will be followed up every month for 3 months after treatment. The primary outcomes include changes in quadriceps femoris muscle area, thickness, vastus intermediate muscle thickness, subcutaneous tissue thickness, and ultrasonic intensities of the rectus femoris. The secondary outcomes consist of the modified Barthel index score and the Medical Research Council total score. Participants' mechanical ventilation, the rate of detachment at the second week, the 28-day survival rate, and the occurrence of adverse reactions will be measured, and any side effects will be reported and recorded. Patient outcomes between the treatment and control groups will be compared and statistically tested. We anticipate that the therapeutic regimen of acupuncture combined with rehabilitation training would be more effective than the rehabilitation training alone for the treatment of the ICUAW. The findings of this study could help develop a better strategy for the treatment of the ICUAW disease and explore a clinical application of an acupuncture technique. Trial registration: Chinese Clinical Trial Register ChiCTR2000038779. Registered 30 September, 2020, https://www.chictr.org.cn/showproj.aspx?proj=62284.

## 1. Introduction

The intensive care unit (ICU)-acquired weakness (ICUAW) is a generalized muscle weakness complication developed during ICU admissions for which no other disease cause can be identified except for acute illness or its treatment. Approximately 40% of ICU patients with a history of at least 48 h of mechanical ventilation develop ICUAW. The disease affects peripheral and respiratory muscles, causing prolonged time of mechanical ventilation and hospital stay, increased hospital mortality, and chronic disability [1–5]. The mechanisms by which ICUAW develops are complex and involve functional and structural alterations in both the muscles and the nerves. Recovery from ICUAW typically takes several weeks or months, and muscle weakness in some patients can last for up to 2 years after discharge from the ICU. Because the pathogenesis of ICUAW is still unclear, there are no specific treatments. The current management of ICUAW includes an active treatment of the primary disease (e.g., sepsis), prevention of infection, control of high blood sugar, reduction of the duration of immobilization, and avoidance of other known risk factors, such as malnutrition, unnecessary application of corticosteroids and neuromuscular blockers, and early rehabilitation [6–8]. Thus, the development of easy-to-perform, more effective ICUAW-targeted interventions is needed for the prevention and treatment of ICUAW.

Acupuncture is a component of the traditional Chinese medicine that is practiced in China as well as abroad as a part of medical care for systemic disease treatment and is believed to work on the principle of the redistribution of “QI,” the life energy concept in Chinese. As per traditional Chinese medicine, diseases result from an imbalance or poor flow of QI. Acupuncture can cure the diseases based on the conduction of meridians and acupoints and following the application of certain operations to improve the flow of QI. In our previous studies, we found that ICU-acquired myasthenia is an acute polyneuromyopathy, and early rehabilitation exercise alone can only reduce physiological dysfunction. Based on our clinical experience on the treatment of various neuromyopathy diseases, we found that acupuncture therapy can improve patients' nerve function [9], restore their muscle atrophy [10] and muscle mass and strength [11], relieve their symptoms, shorten offline time and hospital stay, and improve the quality of patients' lives. In particular, it can significantly alleviate the obvious atrophy of lower limb muscle thickness and cross-sectional area of ICU patients with acquired muscle weakness [12, 13]. More recent studies have found that the combination of acupuncture and speech rehabilitation training improved the total response rate of stroke patients with dysarthria [14]. Based on these studies, we presume that acupuncture and moxibustion combined with rehabilitation training can synergize the effects and offer complementary advantages. The combined therapeutic strategy is superior to simple acupuncture and rehabilitation training alone for the prevention and treatment of patients with ICUAW. However, the efficacy of this therapeutic regimen has not been evaluated yet. To test this hypothesis, we designed a randomized controlled trial with a 3-month follow-up to evaluate whether acupuncture combined with rehabilitation training benefits the recovery of patients with ICUAW and planned to determine the temporal extent of this effect after last successful treatment.

## 2. Methods and Analysis

### 2.1. Design

A parallel-group, randomized, and single-blinded (outcome assessors) prospective clinical trial was designed according to the Consolidated Standards of Reporting Trials (CONSORT 2010) guidelines (Figure 1), Standards for Reporting Interventions in Controlled Trials of Acupuncture (STRICTA) [15, 16], and Standard Protocol Items—Recommendations for Interventional Trials (SPIRIT) statement (Figure 2) [17] and the SPIRIT checklist. Patients with ICUAW will be recruited from the Shanghai General Hospital, which is affiliated to the Shanghai Jiaotong University from October 2020 to September 2023. Participants will be screened based on the inclusion and exclusion criteria; briefed on the purpose, procedures, treatments, and possible risks of the trial; and informed of their rights to discontinue participation in the clinical study at any time point. Once participants will have signed the written consent forms, they will receive either 20 sessions of acupuncture plus rehabilitation training therapy or sham acupuncture plus rehabilitation training for 4 weeks. The study design flow chart and the schedule are presented in Figure 1 and Table 1, respectively. In this study, we will follow the methods of Shou et al. 2020 [18].

### 2.2. Modified Barthel Index (MBI) Score and Medical Research Council (MRC) Total Score

#### 2.2.1. Inclusion Criteria

Participants who would meet all of the following criteria will be enrolled in the study: (1) age >18 years, male and female patients diagnosed with ICUAW; (2) those who were previously admitted to ICU for more than 24 h; (3) acute physiology and chronic health disease classification system II (APACHEII) scores in the range of 8–20 points calculated based on the 12 admission physiologic variables and patient's age and chronic health, as described by Knaus et al. [19]; (4) patients with stable hemodynamics; (5) patients with mechanical ventilation, oxygen concentration [fraction of inspired oxygen (FiO_2_)] < 0.6, and positive end-expiratory pressure (PEEP) < 10 cmH_2_O; and (6) patients who would either themselves and/or their families voluntarily agree to participate in the study and provide signed informed consent.

#### 2.2.2. Exclusion Criteria

ICUAW patients who have or had suffered from any of the following conditions will be excluded from the study: (1) primary neurological and muscular diseases before admission, including brain and spinal cord injury, Guillain–Barre syndrome (GBS), and myasthenia gravis; (2) limb disability and limb instability fracture; (3) malignant tumors; (4) active bleeding; or (5) alcoholic patients who would not stop drinking during the trial.

#### 2.2.3. Elimination Criteria

Enrolled participants will be allowed to withdraw from the study after being subjected to the assigned treatment if they: (1) leave the clinical trial for any personal reasons, (2) experience severe adverse life events that require them to withdraw from the trial, (3) do not fully participate in the treatment or follow-ups, and (4) do not comply with the treatment or fail to provide the information required for evaluation.

#### 2.2.4. Ethics

The study was approved by the Ethics Committee of the Institute of Shanghai General Hospital, which is affiliated to the Shanghai Jiaotong University [(2020)98]. An informed consent form will be prepared and provided to the participants for obtaining their signatures (as stated earlier).

#### 2.2.5. Randomization and Blinding

Participants will be randomly assigned (in a 1 : 1 ratio) to either the treatment group or the control group based on blocked randomization using a randomization table. The table will contain, in a random order, all possible combinations of a small series of figures and assume that patients are randomly assigned to treatment or control groups with equal probability. The order of the interventions assigned to each block will be randomized. The process will be repeated for consecutive blocks until all participants would have been randomized. During the period when the participants will receive the first treatment, they will be given sequential treatment cards from independent researchers to ensure adequate concealment. All participants will be treated separately to prevent communication. Except for acupuncturists, all relevant parties will be blinded to the intervention groups. The implementation of treatments will be performed by two acupuncturists who will use patches prepared by operational assistants. The needles will be applied to every participant in the treatment and control groups. In addition, acupuncturists, operational assistants, and research nurses will be instructed to refrain from communicating with the participants regarding anything that would lead them to determine their group allocation. In addition, outcome evaluators and statistical analysts will be blinded and will not be involved in any part of the design and treatments during the trial.

#### 2.2.6. Acupuncture and Sham Therapy

All research assistants and licensed acupuncturists involved in the trial will receive a 2-day training prior to the onset of the study. Both treatments will consist of 20 sessions over 4 weeks, 5 times per week, and each for 30 min. We plan to treat the patients for 4 weeks because normally our patients would have stayed in ICU for 4 weeks. Briefly, patients will be asked to lie down in a supine position. After sterilization, the 0.25 × 40 mm acupuncture needles (Suzhou Tianxie Acupuncture Instruments Co., Ltd., Suzhou, China) will be inserted to the acupoints of the Jianyu (LI15), Quchi (LI11), Zusanli (ST36), Yanglingquan (GB34), and Biguan (ST31) using a neutral reinforcing and reduced manipulation technique. Each needle will be rotated until the patient experiences the “QI” feeling of soreness, heaviness, and the sensation of distension. The procedure for conducting will be standardized as shown in Table 2. Participants in the control group will receive sham needling at the same acupoints with nested blunt needles. All the procedures will remain the same as the one in the treatment group with the exception of the needles, which will be forced to pierce the fixed pad and reach the skin surface without penetrating the skin. All participants will receive regular rehabilitation training.

### 2.3. Health Education

The conscious participants will be explained about the condition and their current situations, encouraged to have a positive attitude, and will be provided timely feedback on the stability of their vital signs. We plan to divert their attention, arrange visits from their family members, solve their psychological barriers, and eliminate their fears.

### 2.4. Rehabilitation Training

#### 2.4.1. Strategy

Physicians will first assess the tolerance of the patients to rehabilitation treatment. They will repeatedly evaluate whether the patients' oxygen supplies meet the respective consumptions and the conditions of their neurological, respiratory, circulatory, and other systems to determine the exercise mode of rehabilitation. Generally, rehabilitation intervention will be conducted in accordance with the following conditions: (a) maintenance of response to stimulation, having measurable cognitive ability characteristics, understanding of certain commands such as those that instruct them to open/close their eyes, look at people, show their tongues, nod, frown, and others; (b) FiO_2_ < 60%, PEEP <10 cmH_2_O; and (c) lack of orthostatic hypotension symptoms or need to pump vasoactive drugs. All patients will be required to be free of deep-vein thrombosis before the onset of rehabilitation. Physiotherapists will also evaluate the joint range of motion, the muscle strength, tension and endurance, and the ability of activities of daily life prior to the development of a standardized rehabilitation plan.

Physical training will be gradually advanced as follows: passive joints on the bed ⟶ active joints on the bed ⟶ active activity at bedside ⟶ assistance to get out of the bed. These tasks will be conducted 5 days/week. Patients would move on to the next stage only after completing the previous stage of training. If the participant becomes intolerant during recovery or if there is a tendency to change, the training will be stopped immediately.

### 2.5. Passive and Active Motion of Limb Joints

For the participants in coma or continuous sedation and those with limb muscle strengths < Grade III, a passive motion of limb joints will be performed. If the patient muscle strength is zero, we will help them to passively move each joint in both directions 8 times/group, two groups/exercise, 2 times/day, without half normal ranges of motion. If the muscle strength is Grade I or II, we will move the patient's points 8 times/group in 2 directions, and 2 times/group, 2 times/day, based on a normal range of motion. Conscious patients will be encouraged to exercise according to the following regime: clenched fist and double upper limb lifting exercise, double lower limb flexing 90°, straight leg raising 30°, 2 legs of alternate exercise for 10 min, 3 times/day; every 2 h the patients will be asked to turn over to lie on their sides and then sit upright on the bed (e.g., one end of the bed will be elevated). Patients will also be instructed to maintain the seated position if they can for 20 min, 3 times/day; otherwise, we will raise the head of the bed gradually and let the patients maintain the half-sitting position for 20 min, 3 times/day.

### 2.6. Sitting Position on and Beside the Bed

Conscious participants with upper limb muscle strengths of >Grade III will be provided with a back support to sit by the bedside for 10 min the first time, followed by 20 min the second time (provided they can tolerate it the first time), 2 times/day. They will also be helped to sit at the bedside for 1 h during the first-time exercise 2 times/day, followed by a gradually increase of up to 2 h if the patient can tolerate it the first time. The seating angle will be adjusted according to the participants' muscle strength.

### 2.7. Lower Extremity Muscle Exercises

Pet-type conditions will be added to lower extremity muscle exercises, such as bedside bicycle exercises. If the body and lower limb muscle conditions of the participants allow them to stand at the bedside but restrict them to walk, instruments for upper arm support will be provided, and the participants will be helped to stand at the bedside. For the participants with severe neuromuscular atrophy and those who cannot stand without support, “standing bed” will be used to help them stand up for 30 min/time, 2 times/day. For patients with muscle strengths of ≥Grade IV, the physiotherapist, physician, and nurse will coordinate their efforts and assist them to walk in the ward, 2 times/day. The walking distance will be determined according to the participants' tolerance.

### 2.8. Concomitant Care and Intervention

Participants with severe symptoms in both groups will be treated by first-aid kit medications. The type of medicine, dosage, and usage will be recorded on diary cards for analyses. For those with more complicated chronic diseases who must continue to take their routine medication and receive the necessary therapies, the names of the diseases, medications, and therapies used will be recorded.

Our registered nurses will monitor all the patients in the ICU 24 h/day, 7 days/week, and our ICU physicians will examine the patients every 6 h. In case the acupuncture causes hemodynamic instabilities, such as arrhythmias, hypotension, and confusion, the ICU physicians will be called immediately to treat the patients. In most cases, hemodynamic instability would require some type of artificial, mechanical support to maintain the blood pressure and heart activity. For cases in which the participants are unable to receive additional intervention with acupuncture rehabilitation after an evaluation, the participants will be withdrawn immediately from the study and undergo an alternative rehabilitation program. Based on our clinical experience, it is unlikely that patients will have sudden disorders of consciousness or limb twisting; these symptoms are usually experienced by patients suffering from seizures. If such problems arise in Grade I or II sectors of rehabilitation training, the patients will be kept away from the unsafe area and will be allowed to lie on their backs by removing the pillows. Any secretions from the mouth will be removed by turning the patients' heads to one side. Furthermore, ICU doctors will be called to rescue the patients and obtain neurological consultation.

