### 2.9. Discontinuation of the Intervention

The intervention will be terminated in cases with severe adverse events, when participants wish to withdraw from the trial, or when patients use unpermitted medication that would interfere with the recovery outcomes. Patients will have the option to ask the doctor about possible alternative therapies (e.g., nutritional support such as use of tricreatine *β*-hydroxyl-methylbutyrate, antioxidant therapy, and immunoglobulin therapy).

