### 2.14. Follow-Up

The health statuses of the participants after the 4-week treatment period will be followed up on a monthly basis via telephonic and message communications for 3 months based on the previous study for this disease [22]. The symptoms and medication compliance or changes in medication will be recorded. In the event that participants withdrew from the trial or deviated from the intervention protocols, the staff will record the reasons for their withdrawal and the details of their new medications as well as the latest outcome data including the symptoms and frequency of the attacks prior to their exclusion from the study.

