### 2.21. Efficacy Analysis

Efficacy data analyses will be conducted based on the intention-to-treat population. All participants will be initially included in one of the two groups and considered in the statistical analyses. Analysis of efficacy will be conducted for each protocol and include all the participants who would complete the entire research processing. Descriptive statistics will be used to report primary outcome indicators between the two groups. All the data will be statistically analyzed using SPSS. All measurements will be expressed as mean ± standard deviation. The *t*-test will be used for comparisons between two samples if the distributions are normal, and the F-test will be used for comparisons among multiple samples. The Kruskal–Wallis H-rank sum test was used if the distribution is not normal. The participants' sex and course of disease will be recorded, and the data will be tested using the *χ*^2^ test. The ultrasound data will be analyzed by a mixed-effect model. The Cox-regression analysis will be performed to identify outcome-related factors. *P* < 0.05 will be considered as statistically significant.

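### Participants who cannot continue the intervention leave the study, so their week-4 primary outcome goes unobserved despite the intention-to-treat plan, and the completer analysis is open to selection bias

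*Protocol article*

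**What the plan says.** Five places in the protocol article bear on this.

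- **Section 2.8 (Concomitant Care and Intervention).** The paragraph opens with "In case the acupuncture causes hemodynamic instabilities, such as arrhythmias, hypotension, and confusion". For participants then judged unable to have further intervention, it says "the participants will be withdrawn immediately from the study and undergo an alternative rehabilitation program". The exit is from the study, not only from treatment.
- **Section 2.9 (Discontinuation of the Intervention).** "The intervention will be terminated in cases with severe adverse events". Here only the intervention ends.
- **Section 2.2.3 (Elimination Criteria).** The lead-in is "Enrolled participants will be allowed to withdraw from the study after being subjected to the assigned treatment if they". The listed grounds include incomplete participation (item 3) and, in item 4, that they "do not comply with the treatment or fail to provide the information required for evaluation".
- **Section 2.14 (Follow-Up).** For participants who withdraw or deviate from the intervention, staff record reasons, new medication and the most recent outcome data "prior to their exclusion from the study". No later assessment is mentioned.
- **Section 2.21 (Efficacy Analysis).** "Efficacy data analyses will be conducted based on the intention-to-treat population", with all participants considered. Then: "Analysis of efficacy will be conducted for each protocol and include all the participants who would complete the entire research processing". A mixed-effect model is named for the ultrasound data.

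Section 2.23 adds an adjustment for missing data, which it does not specify, and a sensitivity analysis. Section 2.11 sets the primary outcome as the change in ultrasound measures from baseline to the end of the 4-week treatment.

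**The concern.** An intention-to-treat analysis needs outcomes on everyone randomised, including those who stop treatment. Section 2.8 ends study participation because treatment cannot continue, and section 2.14 asks for outcome data only up to exclusion. A participant removed before week 4 therefore has no observed primary outcome, and the gap arises from the plan's own rule rather than from chance.

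Two things are at stake. The intention-to-treat result depends, for these participants, on modelling assumptions about values that could have been measured. And the completer analysis compares groups selected after randomisation. The section 2.8 paragraph concerns instability attributed to acupuncture, and the sham in section 2.2.6 does not penetrate the skin, so it is plausible that removal could differ between arms and be related to prognosis. If both are true, the completer comparison is distorted. A later analysis plan can choose how to handle missing outcomes, but it cannot recover scans that were never taken.

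**Working it through.** **1. The passages side by side**

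| Section | Event | Consequence stated |
|---|---|---|
| 2.8 | Unable to have further intervention | Leaves the study |
| 2.9 | Severe adverse event, wish to withdraw, unpermitted medication | Intervention ends |
| 2.2.3 | Incomplete participation, non-compliance, missing information | Permitted to withdraw, under a heading about elimination |
| 2.14 | Withdrawal or deviation | Data up to exclusion |
| 2.21 | Analysis | All randomised; also completers |

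Stopping treatment ends participation in 2.8 but not in 2.9. Followed literally, 2.8 and 2.14 leave the week-4 value in 2.11 missing for those removed earlier.

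**2. How much loss the plan itself allows**

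Section 2.18.1 takes 23 per group and adds 5 for a possible 20% dropout: 23 × 1.2 = 27.6, rounded up to 28. Five of 28 is 5/28 = 17.9%, and 20% of 28 is 5.6. A loss of 5 in one arm is therefore within what the plan expects. (The stated inputs do not reproduce the 23: a difference of 0.2 with an SD of 0.1 needs only 4 to 6 per group. That is a separate matter and does not decide this point.)

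**3. Size of the completer bias, with no true effect**

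Assumptions, none of them given in the protocol: outcome standardised to SD 1 with higher better; 28 per arm; the *w* frailest participants in each arm withdraw; frailty correlates ρ with poor outcome.

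In large samples, removing the fraction *f* with the worst prognosis raises an arm's mean by ρ × φ(z_f)/(1 − f), where z_f is the *f* quantile of the standard normal.

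- *f* = 5/28: z = −0.921, φ = 0.261, shift = 0.261/0.821 = 0.318 at ρ = 1. Simulation with exactly 28 per arm gives 0.306.
- *f* = 2/28: z = −1.465, φ = 0.136, shift = 0.136/0.929 = 0.147 at ρ = 1. Simulation gives about 0.14.

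The bias is the acupuncture shift minus the sham shift. For 5 against 0 it is ρ × 0.306; for 5 against 2 at ρ = 1 it is about 0.306 − 0.14 = 0.17. Simulated results (20,000 runs per row and correlation):

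| Withdrawn, acupuncture vs sham | ρ = 0 | ρ = 0.3 | ρ = 0.5 | ρ = 1.0 |
|---|---|---|---|---|
| 5 vs 0 | 0 | +0.09 | +0.15 | +0.31 |
| 5 vs 2 | 0 | +0.05 | +0.08 | +0.17 |
| 5 vs 5 | 0 | 0 | 0 | 0 |
| 2 vs 5 | 0 | −0.05 | −0.09 | −0.17 |

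Entries are in SD; plus favours acupuncture; values within simulation error of zero are shown as 0.

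For 5 against 0, the completer t-test wrongly declares acupuncture better in 5.1%, 7.8% and 22.5% of trials at ρ = 0.3, 0.5 and 1.0, against a nominal 2.5% in that direction.

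**4. Against what yardstick**

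With 23 per group, 80% power and two-sided 0.05, the detectable difference is about 0.845 SD, so 0.31 SD is 0.31/0.845 = 37% of it. On the plan's own thickness inputs the target is 0.2/0.1 = 2 SD, and 0.31 SD is 0.31/2 = 16% of that. The relative size depends on which yardstick is used, so the SD figures are the ones to rely on.

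**The case against.** The strongest reply is that the plan names intention to treat first and considers all participants. A completer analysis beside it is routine: the odd phrasing in 2.21 reads as a rendering of per-protocol, and sections 2.19 and 2.23 refer to several data sets. Their ranking could be left to the separate analysis plan announced in 2.23. This stands. Having both analyses is not a contradiction, and a missing ranking alone would not be a finding.

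A reader might also infer that intention to treat becomes impossible. The documents do not support that. The mixed-effect model, the week-2 assessment in Table 1 and the provisions of 2.23 permit an all-randomised analysis from partial data. What they cannot supply is the missing week-4 observation.

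A reader might infer that section 2.2.3 forces non-compliers out. Its wording permits withdrawal; compulsory removal could be read only from its heading together with 2.14. Nor does 2.14 expressly forbid later assessment. Section 2.8, however, is explicit without that support.

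Finally, a reader might infer that the result will be biased towards acupuncture. The 2.8 rule is not limited to one arm, both arms receive rehabilitation, and no rates by arm are given. Step 3 shows the bias vanishing or reversing under other equally unstated patterns.

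**Conclusion.** The point holds for trial conduct. Sections 2.8 and 2.14, read as written, end outcome collection for participants whose intervention stops, and they disagree with 2.9. The intention-to-treat analysis then leans on assumptions for those removed before week 4, and the completer analysis is exposed to selection.

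The bias is conditional. It favours acupuncture only if withdrawal is more frequent in that arm and tied to poor outcome: about 0.05 to 0.15 SD for 5 against 0 to 2 withdrawals at correlation 0.3 to 0.5. The 0.31 SD figure (5 against 0, full dependence) is a one-arm extreme. An even more extreme bound, exactly the worst 20% lost from one arm in a large sample, is 0.280/0.8 = 0.35 SD and should not be taken as an expected size. These figures concern the completer analysis; they do not measure the error of the model-based intention-to-treat analysis.

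It is worth correcting because uncollected outcomes cannot be recovered afterwards. No view is taken on when treatment should stop.

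**What to change.** - Reconcile sections 2.2.3, 2.8, 2.9 and 2.14 so that stopping the intervention and leaving the study are separate events. Leave the clinical stopping rules as they are.
- State that every living randomised participant continues the scheduled week-2, week-4 and follow-up assessments after the intervention stops, unless consent to be measured is withdrawn.
- State that items 3 and 4 of section 2.2.3 (incomplete participation, non-compliance or missing information) are not reasons to remove a participant from follow-up or from the primary analysis.
- In section 2.21, make the analysis of all randomised participants, as assigned, the primary one. Label the completer analysis per-protocol and supportive.

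The cost is protocol wording, plus assessments already in Table 1 for the few participants who would otherwise be dropped: about 5 or 6 per arm at the planned 20% loss. No new procedure is needed and the sample size does not change.
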